#### c) Endpoints

Firstly, we will investigate the beneficial effect of an articulated prosthetic ankle (LUNARIS®) compared to an usual rigid passive foot (SACH®) on functional physical performance by means of a clinical investigation. Secondly, this investigation will examine the differences in brain neuroplasticity and movement patterns according to the type of prosthesis.

#### d) Methods and timing for assessing, recording and analysing variables

##### Population & sample size:

Adults aged 25-65 with a transtibial amputation will be recruited through contacting rehabilitation centres, and orthopaedic departments of hospitals within the network of BruBotics ([BruBotics.eu](https://BruBotics.eu)) and Axiles Bionics ([Axiles Bionics | Next Generation Bionics](https://AxilesBionics.com)). Adults with a Medicare Functional Classification level lower than K3, metal implants, bilateral amputation, additional upper-limb amputation or diabetes will be excluded as well as participants with neurological disorders or with excessive stump pains and wounds. All participants will be asked to provide their written consent after being written and verbally informed regarding the study protocol. The study will be executed in compliance with the Declaration of Helsinki [10] and Ethical approval will be sought from the medical ethics commission of VUB and UZ Brussel.

##### Protocol:

Figure 2 provides a visualisation of the investigation workflow.

[figure not shown]

Figure 2: Overview clinical trial. MRI: Magnetic Resonance Imaging, PEQ: Prosthetic Evaluation Questionnaire, ADL: Activities of Daily Living

The clinical investigation will comprise 4 test days for participants with a lower limb amputation and 2 days for the control group of able-bodied individuals.

The able-bodied individuals will undergo an MRI-scan at the University hospital Brussels (dpt. Radiology and Magnetic Resonance) and then perform functional performance tests.

Participants with a lower limb amputation will start the clinical investigation upon the start of their rehabilitation. At week 0, when initiating the rehabilitation, participants will undergo a baseline MRI-scan at the University hospital Brussels (dpt. Radiology and Magnetic Resonance). Then, they will be allocated to the one of the treatment arms (LUNARIS® or the SACH® foot) and will conduct their rehabilitation to learn walking with a prosthesis. At the end of the rehabilitation, after 12 weeks, participants will perform baseline functional performance tests, fill out the prosthetic evaluation questionnaire (PEQ) measuring quality of life [11] and fill out the Mini-Mental State Examination to account for cognitive impairments and onset of Alzheimer's Disease [12]. Between weeks 12 and 24 of the clinical investigation (i.e. intervention period), participants will perform their daily activities with the allocated prosthesis. During this 12-week period, trying out new prosthetic devices will be allowed within the group of individuals wearing the SACH® foot as this is considered the usual care. At the end of this period (after week 24), post-test assessment will take place and participants will undergo the same MRI and functional performance tests as during the baseline assessments to evaluate the changes that occurred. Additionally, the participant will be asked to fill out the Quebec User Evaluation of Satisfaction with assistive Technology (QUEST 2.0) to assess prosthetic satisfaction [25-27]. The 12-week intervention period is chosen based on a study examining the effect of 12 weeks balance training in healthy and older adults on neuroplasticity and on the accommodation time to walking with a new prosthesis [13][14][15].

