## 5. Objectives and hypotheses of the clinical investigation

### a) The purpose of the clinical investigation

This clinical investigation aims to study the rehabilitation with the LUNARIS® in comparison to the rehabilitation with usual rigid passive feet.

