## 6.4. Procedures

### a) Description of all clinical investigation-related procedures that subjects undergo during the clinical investigation

*Lower-limb amputees:*

There are three measurement moments for lower-limb amputees which will be divided into four days.

**Day 1:** the subject will be expected at the radiology department at UZ Brussel. Here, a non-invasive brain scan will be taken under the supervision of [name]. [name] (department head of Radiology). This measurement moment will take approximately 60 minutes.

**After 12 weeks:** the subject will be expected at Axiles Bionics for a series of non-invasive tests. This measurement moment will take approximately 120 minutes.

**After 24 weeks:** this measurement moment will be divided into two days. The subject will be expected on day 1 at the radiology department at UZ Brussel. Here, the same brain scan will be taken as described in measurement moment 1. This measurement moment will take about 60 minutes. On day 2, the subject will be expected at Axiles Bionics for a series of non-invasive tests as described in measurement moment 2. This measurement moment will take about 120 minutes.

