### b) Descriptive statistics of baseline data

#### *Functional performance testing*

A mixed model will be constructed enabling within and between group (i.e., type of prosthesis) comparison of balance performance and accounting for baseline covariates. If residuals are not normally distributed, required adaptations to the data or model will be performed. To correct for multiple comparisons, suited corrections will be applied. The factors age, time since amputation, side of amputation, level of amputation, time using prosthesis, previously used prosthesis will be accounted for. Statistical significance level will be set at 5%.

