### e) Sample size calculation and justification

The primary endpoint of the clinical trial is the distance covered during the 6-minutes' walk test. The sample size was calculated based on a study comparing passive and quasi-passive prosthetic ankles which found an effect size Cohens'  $f = 0.318$  on distance covered during the 6-minutes' walk test [4]. A total of 40 participants with a lower limb amputation is required and will be allocated to one of the two prosthetic groups. These individuals will be stratified by age (2 strata:  $< 45$  years,  $\geq 45$  years, block size = 4) to control for age-related cognitive deterioration. A matched control-group of 20 able-bodied individuals will be included to enable comparison. The required number of 40 participants with amputation is based on a sample size calculation for an analysis of variance using G\*Power (version 3.1.9.4) envisaging 10% drop-out. Values used for this calculation were medium expected effect size  $f = 0.318$ , power = 0.80,  $\alpha = 0.05$ , the number of groups = 3 and the number of measurements set at 2 with a correlation between measurements of 0.75.

- f) The rationale for the number of procedures to be performed by a single user as part of the learning curves

A baseline experiment with a conventional prosthetic ankle used in rehabilitation is required to observe any similarities or differences in outcomes with the LUNARIS®. Moreover, a baseline experiment with able-bodied subjects is required to observe any similarities or differences in outcomes with the LUNARIS®. Therefore, each lower-limb amputee is asked to schedule four appointments and each able-bodied subject is asked to schedule two appointments to run through the whole experiment.

- g) Pass / Fail criteria to be applied to the results of the clinical investigation

Not applicable.

- h) The provision for an interim analysis

Not applicable.

- i) Management of bias

All appointments for the MRI will take place at UZ Brussel to avoid any bias due to a different MRI scanner. All appointments for functional performance testing will take place at Axiles Bionics to avoid any bias due to different slopes or staircases between subjects and between sessions.

- j) Management of potential confounding factors

Not applicable.

- k) Description of procedures for multiplicity control and adjustment of error probabilities

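### The walking test labelled baseline is taken 12 weeks after allocation, and no primary contrast is fixed, so the plan invites an analysis that removes whatever part of the effect is already present by then

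*Protocol*

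**What the plan says.** Protocol section 6.1 d) sets the order of events. At week 0 participants with an amputation have an MRI. "Then, they will be allocated to the one of the treatment arms (LUNARIS® or the SACH® foot) and will conduct their rehabilitation". The first walking test follows later: "At the end of the rehabilitation, after 12 weeks, participants will perform baseline functional performance tests". The visit list in section 6.4 a) agrees. Day 1 is the scan only, and then "After 12 weeks: the subject will be expected at Axiles Bionics for a series of non-invasive tests". No functional test precedes allocation.

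Section 6.1 d) calls weeks 12 to 24 the intervention period. At week 24 participants repeat the same MRI and "functional performance tests as during the baseline assessments to evaluate the changes that occurred".

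The purpose in section 5 a) is wider: "This clinical investigation aims to study the rehabilitation with the LUNARIS® in comparison to the rehabilitation with usual rigid passive feet". The synopsis (section 1.5) says the same, and section 6.2 a) counts rehabilitation within six months of exposure to the device.

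For the analysis, section 7 b) says: "A mixed model will be constructed enabling within and between group (i.e., type of prosthesis) comparison of balance performance and accounting for baseline covariates". It lists the factors to be accounted for, and week-12 distance is not one of them. It does not say whether the primary result is the arm difference at week 24, the arm effect over both visits, or the arm-by-visit interaction.

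**The concern.** A baseline value is useful because the treatment cannot have affected it. Here the value so labelled is the primary endpoint itself, measured after 12 weeks on the allocated foot. Any benefit gained during rehabilitation is already in it. Subtracting it removes that benefit from the estimate, and adjusting for it removes much of it. What remains answers a narrower question: what is added between weeks 12 and 24, after the rehabilitation that the trial says it studies has ended.

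The label also means two things. For MRI, baseline is week 0, before allocation. For function it is week 12, after it. Change therefore covers 24 weeks for the brain and 12 weeks for walking, although section 7 b) relates brain structure to performance in one model.

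In the SACH arm, trying other devices is allowed during weeks 12 to 24, so change in that arm mixes time with a possible change of foot.

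**Working it through.** **The plan's own figure.** Sections 5 c) and 7 e) require 40 participants with an amputation, from f = 0.318, power 0.80, alpha 0.05, 3 groups, 2 measurements, correlation 0.75 and 10% drop-out. If this figure reproduced for one contrast, it would show which contrast was meant. It does not. Noncentral F calculations for repeated-measures ANOVA give these totals, with the drop-out-inflated total in brackets:

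- 3 groups: interaction 18 (20); between-group effect 87 (97)
- 2 groups: interaction 12 (14); between-group effect 70 (78)

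So the sample size does not settle the contrast. That mismatch is a separate matter, and nothing below depends on it.

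**Inputs from the protocol.** Effect of interest 35 m (sections 5 d and 6.1 e); correlation 0.75 (7 e); 20 per prosthetic arm (6.1 a), or 18 after 10% drop-out.

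**Assumptions.**
- s, the share of the week-24 effect already present at week 12, ranges from 0 to 1.
- The SD is the same at both visits. Reading f as half a standardised two-arm difference, SD = 35/(2 x 0.318) = 35/0.636 = 55 m. The protocol states no SD.
- The arms are comparable apart from the device.

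**Expected estimate.**
- Change from week 12, or arm-by-visit interaction: 35 - 35s = 35(1 - s)
- Adjustment for week 12: 35 - 0.75 x 35s = 35(1 - 0.75s)
- Arm difference at week 24: 35

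**Spread, as a multiple of the SD.** Change: √(2 x (1 - 0.75)) = 0.707. Adjusted: √(1 - 0.75²) = 0.661. Week 24: 1.

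Power below is from 20,000 simulated trials (two-sided 5%), for 18 / 20 per arm:

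| s | Change, m | Adjusted, m | Week 24, m | Power: change | Power: adjusted | Power: week 24 |
|---|---|---|---|---|---|---|
| 0 | 35 | 35 | 35 | 74% / 79% | 78% / 83% | 46% / 50% |
| 0.5 | 17.5 | 21.9 | 35 | 26% / 29% | 40% / 44% | 46% / 50% |
| 0.75 | 8.8 | 15.3 | 35 | 10% / 11% | 22% / 24% | 46% / 50% |
| 1 | 0 | 8.8 | 35 | 5% / 5% | 10% / 11% | 45% / 50% |

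**Thresholds.** A change score loses more than half the effect only if s > 0.5. Adjustment loses more than half only if 0.75s > 0.5, that is s > 0.67, and never more than 75%. On power, the week-24 contrast overtakes change at about s = 1 - 0.707 = 0.29. It overtakes adjustment at about s = (1 - 0.661)/0.75 = 0.45, ignoring a small extra variance term.

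**The case against.** The strongest reply is that the protocol does not commit to the harmful analysis. Section 7 b) plans comparisons within and between groups and does not list week-12 distance as a covariate. H1 (section 5 d) and the 35 m criterion (section 6.1 e) are worded as differences between prostheses. A mixed model with both visits as outcomes fits section 7 b) as written, and the exact contrast is often left to the SAP. This largely stands: the fault is a mislabelled visit and an open contrast, not a wrong test already specified. It does not dispose of the point, because the protocol itself calls the visit baseline and ties the evaluation of change to it.

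A reader might infer that most or all of the effect is lost. The documents do not support that, because s is not given. The 12 weeks were chosen partly with accommodation to a new prosthesis in mind, which makes a large s plausible but does not establish it. Total loss cannot follow from adjustment at a correlation of 0.75 with equal SDs.

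A reader might also see a contradiction in section 7 f): "A baseline experiment with a conventional prosthetic ankle used in rehabilitation is required to observe any similarities or differences in outcomes with the LUNARIS". The next sentence asks in parallel wording for a baseline experiment with able-bodied subjects, which means a reference group. The sentence can likewise mean the SACH group. It does not say that LUNARIS participants are tested on a conventional foot.

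The purpose is not stated uniformly either. RO.1.1 (section 5 b) speaks of walking performance with the two devices and does not mention rehabilitation. This strengthens the case for naming one estimand.

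Lastly, section 6.3 e) says allocation is not randomised. A change score would cancel stable differences between the arms that have nothing to do with the device, and the week-24 contrast does not. That is a real cost, but the same subtraction cancels the device effect already present at week 12.

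**Conclusion.** The point holds in this form. The functional test called baseline is a post-allocation outcome, and the primary contrast is not fixed. An analysis that follows the label would miss whatever part of the effect arose during rehabilitation: all of that part under a change score or interaction, and three quarters of it under adjustment. For a 35 m effect the estimate falls to between 35 and 0 m, or between 35 and 8.8 m, depending on s.

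The metre figures rest on the range for s and, for adjustment, on the correlation of 0.75 and equal SDs. The power figures also assume an SD of about 55 m and comparable arms. At s = 1, power is about 5% for change, 10-11% adjusted and 46-50% for the week-24 contrast. At s = 0 the order reverses: 74-79%, 78-83% and 46-50%. The case for the week-24 contrast is therefore that it estimates the stated effect at every s, not that it always has the most power. The matter should be settled before analysis, because it decides what the primary result means.

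**What to change.** - Rename the visit the week-12 assessment, and keep the word baseline for measurements made before allocation.
- State the primary estimand as the between-arm difference in mean 6-minute walk distance at week 24.
- Estimate it from a mixed model with week-12 and week-24 distances both as outcomes (arm, visit, arm x visit). Report the week-12 contrast and the week 12 to 24 change as secondary.
- In the primary analysis, neither subtract nor adjust for week-12 distance.
- Adjust only for variables known before allocation. This is needed because allocation is non-randomised. Time using prosthesis needs a stated reference date, since counted at the test it runs on after allocation.
- Reconcile sections 5 a), 5 b) and 6.1 d) on whether the effect studied starts at week 0 or week 12.
- Clarify, rather than delete, the section 7 f) sentence by naming the group it refers to.

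The cost is wording in the protocol and SAP; visits and data stay the same. There are two limits. If little of the effect is present by week 12, the week-24 contrast has less power than a change analysis. It also removes neither confounding by unmeasured differences between the arms nor the influence of permitted device changes in the SACH arm, and the report should say so.

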## 6.2. Investigation device(s) and comparator(s)

### a) Description of the exposure to the investigational device

20 subjects are asked to do their rehabilitation process with the LUNARIS® and then to perform their daily activities with the LUNARIS® during a period of 6 months in total. They are also asked to perform the above mentioned activities with the LUNARIS® during 2 experimental sessions.

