### b) List of any other medical device or medication to be used

20 subjects are asked to do their rehabilitation process with an usual rigid passive foot (SACH®) and then to perform their daily activities with the most suited prosthesis for them during a period of 6 months in total. They are also asked to perform the above mentioned activities with the most suited prosthesis for them during 2 experimental sessions.

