#### *Structural brain adaptations*

Differences in connectivity between pre-test and post-test assessment, both within and between groups (i.e. type of prosthesis), will be analysed by means of structural equation modelling. This analysis allows to investigate the causal relationships between brain structure and performance indicators while controlling for confounding factors. The factors time since amputation, side of amputation, amputation level, time using prosthesis, previously used prosthesis, age, sex, Mini-Mental State Examination score, and level of education will be accounted for. Statistical significance level will be set at 5%.

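### The cognitive score adjusted for as a confounder in the MRI model is first taken at week 12, after allocation and 12 weeks on the allocated foot

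*Protocol*

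**What the plan says.** The order of events is in section 6.1d, under Protocol. The first scan comes at entry: "At week 0, when initiating the rehabilitation, participants will undergo a baseline MRI-scan at the University hospital Brussels". Allocation follows: "Then, they will be allocated to the one of the treatment arms (LUNARIS® or the SACH® foot) and will conduct their rehabilitation". The cognitive test comes at the next visit, which opens with "At the end of the rehabilitation, after 12 weeks, participants will perform baseline functional performance tests". At that visit participants also "fill out the Mini-Mental State Examination to account for cognitive impairments".

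Section 6.2a confirms that the rehabilitation is done on the allocated device: "20 subjects are asked to do their rehabilitation process with the LUNARIS". Section 6.2b says the same of the comparator group and the rigid foot. Section 6.4a lists only a brain scan at the first visit and places the test series at week 12. The eligibility criteria in sections 6.3a and 6.3b contain no cognitive test.

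Section 7b, under Structural brain adaptations, analyses the pre-test to post-test difference in connectivity, within and between prosthesis types, by structural equation modelling. It presents the adjustment factors as confounders, and the list ends with "Mini-Mental State Examination score, and level of education will be accounted for".

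**The concern.** A confounder of the foot's effect has to describe the participant before the foot can have acted. This score is collected after allocation and after 12 weeks of use.

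Two things are at stake. First, section 6.3e says allocation is not randomised, so the brain comparison leans on covariate adjustment to deal with differences between the groups at entry. A week 12 score is an imperfect record of cognition at entry. Second, if the foot, or rehabilitation that differs in effect between groups, moves the score, then holding the score constant can remove part of the prosthesis effect or introduce bias.

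The analysis plan cannot repair this afterwards, because a week 0 score that was never collected cannot be recovered.

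**Working it through.** The plan gives no figure on this point to reproduce. The check is of timing, followed by an illustration of scale on assumed values.

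**1. Timeline for participants with an amputation**

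| Time | Event | Protocol section |
|---|---|---|
| Week 0 | First MRI; no cognitive test listed | 6.1d, 6.4a |
| After that scan | Allocation to a foot | 6.1d |
| Weeks 0 to 12 | Rehabilitation on the allocated foot | 6.1d, 6.2a, 6.2b |
| Week 12 | Functional tests, PEQ, first MMSE | 6.1d |
| Week 24 | Second MRI, functional tests, QUEST 2.0; MMSE not named | 6.1d, 6.4a |

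The modelled change runs from week 0 to week 24. The covariate is taken 12/24 = one half of the way through that interval, after allocation.

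**2. What the score can say about entry**

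Write the week 12 score as M12 = M0 + r, where M0 is the score at entry and r is the change over the 12 weeks on the foot. The difference between groups is then

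difference in M12 = difference in M0 + difference in r.

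Only the left side is observed. The difference in M0, which is what adjustment for confounding needs, cannot be separated from the difference in r.

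**3. What adjustment can do to the estimate**

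Take a linear model in standardised units, with A the foot, M the week 12 score and Y the connectivity change:

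M = cA + u; Y = dA + bM + e.

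The total effect of the foot is d + bc. After adjustment for M the coefficient of A is d, so bc is removed. This assumes that u and e are unrelated; a shared cause of the two would add a further bias of unknown sign.

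The documents give neither b nor c. On assumed values:
- c = 0 (no effect of the foot on the score): 0 SD removed, whatever b is.
- c = 0.1, b = 0.2: 0.1 × 0.2 = 0.02 SD.
- c = 0.5, b = 0.5: 0.5 × 0.5 = 0.25 SD.

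This shows the form of the problem and is not evidence of its size. A rehabilitation effect equal in both groups gives c = 0 and removes nothing from the between-foot comparison.

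**4. After the fix**

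A score taken before allocation cannot have been affected by the allocated foot. So c = 0 by design, and adjustment removes 0 SD of the prosthesis effect.

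**The case against.** The best defence is that week 12 is the protocol's own baseline. Section 6.1d gives that label to the week 12 functional tests and calls weeks 12 to 24 the intervention period. H2 in section 5d is stated after 12 weeks, and section 6.1e mentions a mid-study MRI. In that framing a week 12 MMSE precedes the intervention. What stands is that the protocol does not use one baseline throughout. It does not rescue the MRI model: sections 6.1d and 6.4a schedule scans only at weeks 0 and 24, and the functional model in section 7b does not list the MMSE. Even a scan at week 12 would come after allocation and 12 weeks on the foot. Figure 2 is not shown and could place a test elsewhere, but its legend does not mention one.

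A second defence is that the model's details may be left to the analysis plan. That is true of how the score enters the structural equations, but visit timing is fixed here.

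Three stronger readings are tempting, and the documents do not support them.

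- A reader might infer that H2 itself puts the score on the causal path. H2 links the foot to structural networks, and networks to physical test performance. It does not mention cognition, and section 6.1e chooses the brain regions for motor control and balance.
- A reader might point to a reference cited for the 12-week period, whose title reports memory gains from balance training. Both groups undergo rehabilitation, so this gives no reason to expect the score to differ by foot.
- A reader might infer that late testing costs participants, because those who leave before week 12 have a scan but no score. They would also lack the week 24 scan, so they have no change to analyse, and section 7m excludes drop-outs. Moving the test would not bring them back.

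**Conclusion.** The point holds as a matter of covariate timing. The plan treats as a confounder a score first taken after non-randomised allocation and 12 weeks on the allocated foot. That score cannot cleanly show cognitive differences at entry. It could bias the between-foot comparison of connectivity change if the foot, or rehabilitation acting differently in the two groups, affects it.

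The effect is probably small. The participants are 25 to 65 years old and neurological disorders are excluded. The documents give no value for either path and no specific reason to expect the score to differ by foot, so the range in the working rests wholly on assumption and includes zero. Only the secondary aim (RO.2, H2) is affected; the six-minute walk analysis is not. This is a minor improvement to the design and does not threaten the trial's main conclusion.

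The conclusion assumes that the text of sections 6.1d and 6.4a gives the full visit schedule, and that the modelled change is between the week 0 and week 24 scans.

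**What to change.** In section 6.1d, move the MMSE to the week 0 visit, with the baseline MRI and before allocation. In section 7b, state that the adjustment uses this week 0 score. If a week 12 score is still wanted, keep it as descriptive only and out of the adjusted model. Update the first visit in section 6.4a to match.

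The cost is modest but not zero: a few extra minutes at a radiology visit now planned at about 60 minutes, someone there able to give the test, and a protocol amendment through the route in section 9. No visit is added and no sample size changes.
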